### **3. Study Procedures**

#### **5.1 Study Design**

**5.1.a. ASAP Overview** The ASAP project will be conducted as a Hybrid Type I, randomized, stepped-wedge trial at 6 intervention sites and 30 control sites over a 3.5-year period (Figure 1). The 6 intervention sites will begin the 21-month active implementation period; (orange shading for WAVE 1, green shading for WAVE 2 and yellow shading for WAVE 3) in 3 staggered “steps” with 2 sites per step. Immediately following the active implementation phase for WAVES 1 and 2 will be a sustainability phase up to 7 months in duration (purple shading). WAVE 3 will not have a sustainability phase. This design allows for 3 active implementation data periods of 7-months duration for each WAVE. As seen in Figure 1, there are a variable number of 7-month data periods in the baseline and the sustainability periods by wave. The ASAP quality improvement intervention includes a systems redesign Virtual Collaborative and data monitoring. As part of the quality improvement intervention, sites will locally tailor and implement an ASAP approach, in which each site chooses a diagnostic strategy from a menu that includes unattended PSG, in-laboratory PSG, or direct to auto-PAP approach. Similarly, sites may choose any treatment strategy.

Figure 1. ASAP Project Active Implementation and Sustainability Timeline

[figure not shown]

**5.1.b. Participating Sites** To be eligible for inclusion in ASAP a site had to have >50 stroke/TIA patients per year and have at least 1.0 FTE staff dedicated to systems redesign. The sites were chosen because they are diverse in terms of geography and sleep infrastructure. Data regarding the capacity to perform acute OSA assessment at each site is included in site investigators' letters of support. Furthermore, the sleep clinical champions vary across the sites and include clinicians trained in pulmonary, neurology, and psychiatry; some have on-site sleep laboratories whereas others use unattended PSG or fee-basis for their PSGs.

Table 2 data provide the estimates that were used in the revised power calculations: 111 patients per year will be eligible.

| VAMC (Site)       | Annual Patient Volume (n) a | History of OSA (n) | PSG in prior 5-years (n) | Potentially Eligible (n) b |
|-------------------|----------------------------------------|--------------------|--------------------------|---------------------------------------|

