**Audit and Feedback** As described above, active implementation sites will receive monthly feedback on quality indicators for ASAP-related process and outcome data. To support the sites' use of data, the local teams will receive explicit training in team-based reflecting & evaluating, goalsetting, and planning. Meeting as a group, local teams will be encouraged to formally ask and answer questions like: "How are we doing?" "Are we where we want to be?" "What performance goals do we want to set as targets?" "What do we need to do to achieve our goals?" "How will we know how far or how close we are to hitting our targets?" The audit and feedback implementation strategy is a key element of the ASAP approach to sustainability, as the activities of reflecting & evaluating, goal setting and planning allow local teams to engage in continuous improvement, stepping back as a group on a periodic basis to review data related to the trajectory of their progress over time, make adjustments as needed to address any dips in performance, and consider how to sustain improvement. Hub usage data will also be collected and summed by site in order to determine how often each month the hub is accessed by each site to audit their own performance.

**5.1.e. Site Randomization** As described above, the ASAP study will be conducted as a stepped-wedge trial with six sites randomly allocated to receive the intervention in three steps, two facilities at a time. At the start of the study, the order in which sites will receive the ASAP program will be derived from a computer-generated randomization list created by ASAP senior statistician ([name]).

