### **5.7 Data Analysis**

**5.7.a. Data Analysis Overview** A stepped-wedge trial will be used, rather than an individual patient-level randomized trial, because the intervention program is implemented at the site-level. Although this trial could have been set-up as a parallel cluster randomized trial (CRT), we sought to examine the treatment effect of the ASAP program using fewer sites (given the resource constraints of the IIR program). Additionally, we chose the stepped-wedge design, as opposed to a before and after within each cluster design, because the latter approach may be biased, (e.g., if underlying rates of OSA diagnosis change during the study period). With a stepped-wedge we can account for the time-related trends by incorporating time as a covariate. Time may be included in the analysis as a categorical variable (i.e., allowing a time effect at each step), or using time as continuous variable (assuming a linear increase or decrease over time).

**5.7.b. Period Classification** The stepped-wedge design allows for 8 mutually exclusive, 7-month data periods. Effectiveness outcome data for each site for each data period will be classified as either control or intervention. The active implementation period will be considered as the intervention phase. If a patient has more than one stroke/TIA, then only the first will be included in the analysis (i.e., patients in each time increment are unique). If a patient has more than one stroke/TIA event, but one occurs in the baseline period and one during the active implementation period, then the event during the active implementation period will be used. The stepped-wedge design allows site-level estimates of

proportions on 8 different cross-sectional samples. Thus, we will have repeated information on each site.

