**5.7.c. Specific Aim 1 (Effectiveness) Analyses** Program effectiveness will be evaluated by a single, primary outcome (diagnostic rate). The diagnostic rate is defined as PSG completion within 30 days of presentation for the index stroke or TIA. **Effectiveness Outcome Ascertainment** We will seek to iteratively improve the CDW algorithms by comparing data to that of the chart review data (e.g., NIHSS data). COVID-19 data has been added to our ASAP administrative data set. COVID-19 data will consist of a combination of: (1) patients with polymerase chain reaction or antigen test results positive for severe acute respiratory syndrome coronavirus 2 (SARS-CoV-2) and; (2) from the VA National Surveillance Tool (NST). Also, pertinent dates related to the impact of the Philips Respironics Recall, indicating VHA-wide availability of PAP, have been added to our data.

Admissions for ischemic stroke and TIA to VAMCs have shown a decline during the COVID-19 pandemic. Furthermore, patients admitted to a VAMC with COVID-19 are not candidates to receive positive airway pressure (PAP) during the index hospitalization.

In considering analyses of the primary outcome, a sensitivity analysis will include re-running the final model with the inclusion of a facility-level, time-varying measure of COVID-19 burden. Although, inclusion of control sites which allows us to adjust for secular time trends may be sufficient to account for the effect of COVID-19 in the model.

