### **Diagnostic Rate**

(Power for Diagnostic Rate: Active Implementation versus Baseline)

Using a stepped-wedge with 6 VA sites, 8 total time points, 2 sites switching at each step, and approximately 64 patients per site ( $111 \times 7/12$ ) at each step, we should have over 90% power to detect a difference in diagnostic rate of 7% and 15% while varying the coefficient of variation (or intra-cluster correlation). 7% was the observed diagnostic rate in FY2017, and intervention is expected to increase the diagnostic rate to 70% so we are appropriately powered for this primary outcome. The detectable intervention diagnostic rate is provided in the table based on the two-sided test statistic while varying the coefficient of variation. We additionally ran 1,000 simulations with varying treatment effects, including a large random site-effect  $u_j \sim N(0, \tau^2)$ , with  $\tau^2$  based on ICC (.03, .05, .20), a linear time-effect ( $\gamma = 0.005$ ), and assuming a diagnostic rate in the control phase of 7%. We then fit the proposed linear mixed model with time as a categorical variable. Even in the extreme case that our ICC is large (ICC = 0.2), we are still adequately powered to detect the difference in diagnostic rate of 7% and 15% (Table 3). This initial power calculation was revisited to include additional baseline data and a slight reduced sample size because of the COVID-19 pandemic. The results of the updated power calculation did not differ substantively from the initial (above) power calculation.

**Secondary Analyses Effectiveness** The three secondary effectiveness outcomes are 30-day treatment rate, 90-day recurrent vascular event rate and 90-day all-cause readmission rate.

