## **Analysis of the Primary Effectiveness Outcome**

### **Diagnostic Rate Analysis**

A generalized linear mixed model will be fit to the patient-level outcome of diagnostic testing (yes/no) to conduct facility-level inference. The primary effect of interest is the effect of the intervention during active implementation versus baseline. Control sites are included to add accuracy in estimation of the secular time trend. A non-exact match approach is planned for this analysis (i.e., unconditional) since this model is being fit to patient-level data which will be used to conduct facility-level inference and there is no guarantee that patients in control sites that were loosely matched to an intervention site using facility factors are similar. This approach will use all available control site data without pairing specific control sites to each ASAP site. Effects in the model include a site-level indicator of intervention site vs control site, indicator for each site and data period corresponding to active implementation or sustainability phase, and time (as categorical, indicating each 7-month data period). The model will also include a random intercept for site to account for potential correlation among patients from the same site. Our interest is in testing the effect of the ASAP intervention on the proportion of patients who are diagnosed at the site-level. This model will also be fit adjusting for any important patient covariates (i.e., stroke severity). Both unadjusted and adjusted results will be reported. Contrasts from the model will also be estimated. All statistical tests will be two-sided, with p-values < 0.05 considered statistically significant. All analyses will include checking of assumptions and model fit.

**Analysis of Secondary Outcomes** As described above, because the treatment rate can only be assessed among the patients who have been diagnosed, we will be limited in our analysis of treatment. If several patients are diagnosed in the during the control phase (which is unlikely), we would use the same mixed model approach as with other outcomes. However, because we expect to have very

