sparse data for the baseline phase, we plan to collapse data within each site across the baseline phases and the treatment phase and compare the within site treatment rates using a permutation test. Doing so will randomly flip the treatment labels of site-level treatment rates. Because there are 6 sites, there are  $2^6$  possible permutations of the treatment labels within pairs. The p-value will then be the proportion of permutations that lead to a test statistic at least as extreme as the actual data. Additionally, we will report the estimated site-level treatment rate during the baseline and intervention phases as well as the associated 95% CIs. We will also compare the overall treatment rate among all patients in the baseline phase to all patients in the active implementation phase using Fisher's exact test.

**90-day Recurrent Vascular Event Rate and Readmission Analysis** will be analyzed similarly to the primary outcome with the exception that the 7-month code-red data period (beginning 9/2021) will not be included. Models for the secondary outcomes (excluding treatment rate) will be fit without covariates (unadjusted) and additionally including patient-level factors (adjusted).

**Missing Data** Because we are using centralized chart review augmented by data from the CDW to collect our baseline characteristics and outcome data, we expect to have very little missing data. Only a few of the patient-level variables which may be included in the models adjusting for covariates may contain a small amount of missing such as stroke severity (as measured by the NIHSS). The amount of missing will be examined before deciding on the handling of missing data. Either complete-case or multiple-imputation will be used for models adjusting for patient-level factors. In the highly unlikely event that for a certain time period we are not able to get data from a specific site, the mixed effects model allows us to still use data for the other time periods for that site. The proposed mixed model methods are appropriate as long as data are missing completely at random (MCAR) or missing at random (MAR). If for any reason, we suspect the pattern of missing data is non-ignorable, more complex modeling approaches may be used.

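### The protocol calls several control-phase diagnoses unlikely and so collapses the treatment-rate analysis, but its own planning figures imply roughly 38 to 93 of them

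*Protocol*

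**What the plan says.** All references are to the protocol.

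- **30-day Treatment Rate** (section 5.7.c): the denominator is newly diagnosed OSA. Data are to be collapsed over control periods and over intervention periods within each site, because few or no baseline OSA patients may receive treatment.
- **Analysis of Secondary Outcomes**: a conditional alternative. "If several patients are diagnosed in the during the control phase (which is unlikely), we would use the same mixed model approach". The next sentence returns to collapsing, because the authors expect "sparse data for the baseline phase, we plan to collapse data within each site across the baseline phases and the treatment phase". The tests named are a within-site permutation test over 2^6 label flips and Fisher's exact test on all patients pooled.
- **Diagnostic Rate** (power): "7% was the observed diagnostic rate in FY2017", with "approximately 64 patients per site" at each step.
- **Section 5.7.c**, definition: "The diagnostic rate is defined as PSG completion within 30 days of presentation for the index stroke or TIA". The 7% therefore counts completed tests, not positive results.
- **Introduction**: OSA prevalence after stroke/TIA is 70-80%.
- **Specific Aim 1**: hypothesised treatment rate of 50% for intervention against 2% for controls, with no denominator stated there.
- **Section 5.7.a**: a before-and-after comparison within clusters was rejected because it may be biased when underlying rates change over time.

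**The concern.** The choice of method for a named secondary outcome rests on how many patients are diagnosed in the control phase. The protocol calls several such patients unlikely, yet powers the trial on a 7% control-phase testing rate in well over a thousand patient-records under the current design. If the premise is wrong, the stated condition for the mixed model is met and the sentence after it sends the analyst the other way. The word several carries no number.

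The two routes differ in substance. The mixed model adjusts for period and uses the control sites. The collapsed tests reduce the trial to six before/after pairs, and Fisher's test also ignores site clustering. Treatment is the outcome most exposed to calendar time here: the protocol itself describes COVID-19 and a PAP recall that affected device availability.

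**Working it through.** **1. Reproduce the plan's own figure.** Patients per site-period: 111 x 7/12 = 64.75, which the protocol gives as about 64. I use 64.

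**2. Count baseline site-periods.** Figure 1 is not shown, so the layout is inferred from these statements:
- "The stepped-wedge design allows for 8 mutually exclusive, 7-month data periods"
- "six sites randomly allocated to receive the intervention in three steps, two facilities at a time"
- "This design allows for 3 active implementation data periods of 7-months duration for each WAVE"
- one 7-month sustainability period for Waves 1 and 2, none for Wave 3

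Three layouts bracket the answer:
- *Central*: one-period steps with Wave 3 ending at period 8, so baselines of 3, 4 and 5 periods. 2 x (3+4+5) = 24 site-periods.
- *Upper*: every period that is neither active nor the single sustainability period counts as baseline, so 4, 4 and 5. 2 x 13 = 26.
- *Lower*: six periods (the 3.5 years in section 5.1.a = 42 months = 6 x 7), baselines 1, 2 and 3. 2 x 6 = 12. This layout also reproduces Table 3: at 15% the computed power is 0.951, 0.935 and 0.925 against the printed 0.95, 0.93 and 0.93.

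**3. Expected newly diagnosed baseline OSA at the six sites** = site-periods x 64 x 0.07 x prevalence (0.70 to 0.80).

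| Site-periods | Tests completed | New OSA |
|---|---|---|
| 12 | 53.8 | 38-43 |
| 24 | 107.5 | 75-86 |
| 26 | 116.5 | 82-93 |

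In the central layout that is about 13 per site and about 3.4 per site-period (64 x 0.07 x 0.75).

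**4. Stress the result.**
- The 7-month code-red period is dropped for this outcome. If it falls in the baseline of two or four sites in the central layout, 22 or 20 site-periods remain: 63-79 diagnoses. In the lower layout, 8 to 10 remain: 8 x 64 x 0.07 x 0.70 = 25 up to 10 x 64 x 0.07 x 0.80 = 36.
- If only 50% of tests were positive (my assumption), 12 to 24 site-periods give 27-54.
- At an expected 38, the Poisson chance of fewer than 10 is about 2 in 100 million.

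**5. Treated baseline patients, the other reason for collapsing.**
- 2% of newly diagnosed OSA: 0.02 x 38 to 0.02 x 93 = 0.8 to 1.9 patients in all.
- 2% of all eligible patients: 12 x 64 x 0.02 = 15 to 26 x 64 x 0.02 = 33 patients.

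**6. What the collapsed test does under a time trend.** I simulated no intervention effect in the central layout: testing 7% at baseline and 70% in active periods, 75% positive, and the chance of treatment after diagnosis rising linearly over 8 periods. The trends are assumptions, not protocol figures. The two-sided permutation test at 0.05 rejected in 3% of trials with no trend (30% throughout), 20% with a rise from 30% to 50%, and 41% with a rise from 20% to 50%.

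**The case against.** The strongest reply is that sparsity of treated patients, not of diagnosed patients, is the real reason for collapsing, and the 30-day Treatment Rate paragraph says so. This stands in part. If the 2% is of diagnosed OSA, one or two treated baseline patients are expected, and the chance of none is about 20% at an expected 1.6 and 42-47% in the lower layout. With none, the model's active-phase effect cannot be estimated stably, and control sites do not cure that. A fallback keyed to the number diagnosed would miss the problem. But the sentence that sets the condition is written on patients diagnosed, and for them the premise is wrong.

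Two stronger readings are tempting and not supported:
- *That the protocol leaves the method undetermined.* It does not. Both paragraphs name collapsing as the default, and the treatment rate is excepted from the covariate and COVID-burden models. What exists is one conditional sentence whose condition, on the protocol's figures, contradicts the default.
- *That the 7% rate implies about 80 diagnoses.* That is one value in a range. It needs an inferred layout and population prevalence used as test yield, with no deduction for the code-red period, the COVID-19 fall in admissions, or exclusions such as central apnea.

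It is also fair that 3.4 diagnoses per site-period is thin for a model with categorical periods. That argues for fixing the rule now. It does not make several diagnoses unlikely.

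**Conclusion.** Wrong as written. On the protocol's own inputs, several control-phase diagnoses are near certain: roughly 38 to 93 at the six sites, 75 to 86 in the central layout, and about 25 in the least favourable case with the code-red period removed. The stated condition for the mixed model is met, yet the text directs an unadjusted before/after comparison of the kind section 5.7.a warns against. The conclusion rests on 7% testing, 64 patients per site-period and 70-80% of completed tests being positive; it survives a 50% yield.

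It does not follow that the mixed model will be stable. That depends on the number treated at baseline, which the protocol leaves between about 1-2 and 15-33 because it does not tie the 2% hypothesis to a denominator. The size of any bias is unknown; the 20% and 41% false-positive rates illustrate assumed trends only. The outcome is secondary, so the primary conclusion is unaffected.

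**What to change.** 1. In Analysis of Secondary Outcomes, delete the statement that control-phase diagnoses are unlikely, and delete the unquantified trigger.
2. Reconcile that paragraph with the 30-day Treatment Rate paragraph, and state in Specific Aim 1 whether 50% and 2% are of newly diagnosed OSA or of all eligible patients.
3. Name the mixed model with period effects and control sites as the primary analysis of the treatment rate.
4. Keep the within-site permutation test as the fallback if the number of treated baseline patients at the ASAP sites falls below a figure fixed now. Note beside it that the smallest two-sided p-value with six sites is 2/64 = 0.031.

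The cost is wording only, since the model is already specified for the other outcomes. The small downside is that a fallback remains necessary, because the model may be unstable if baseline treatment is near zero.

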#### **5.7.d. Specific Aim 2 (Implementation) Analysis**

##### **Interview Administration and Analysis of Implementation Data**

**Interviews** (with staff/providers, and Veterans) will address the planned approach for ASAP implementation (e.g., unattended PSG), local context related to stroke/TIA patient care, local champions, plans to coordinate the care of Veterans across services, and how best to incorporate systems redesign personnel throughout the intervention and sustainability phases (at WAVE 1 and 2 sites). Participating staff/providers will also receive invitations to complete an online version of the Organizational Readiness for Change Assessment (ORCA). The ORCA will be used to more thoroughly understand the readiness of each VAMC from the perspective of each PI across the primary scales of evidence, context, and facilitation and their subscales; of particular interest will include subscales of context (e.g., leadership practice and resources). Follow-up semi-structured interviews will be collected by telephone or virtually immediately after the active implementation period and again at the end of sustainability. Elements from ORCA facilitation subscales will be investigated at the follow-up period (e.g., senior leadership management characteristics, resources) as well as the aforementioned context subscales. These interviews will be audio-taped, transcribed verbatim, and reviewed by investigators to ensure accuracy of transcription. We will develop detailed case studies and timelines to integrate and analyze data related to each site's specific approach to developing and refining a site's acute sleep apnea testing and treatment program. Transcripts, case studies, and timelines will be imported into the software program NVivo, which will be used to support the qualitative data analysis, including coding, analysis, and memo-writing.

Throughout the qualitative data analysis process, investigators will write analytic memos to document the evolution of the analyses, the emergence of early patterns and possible findings, the convergence of major themes, the challenges posed by the analysis, and ideas related to hypothesis testing; these analytic memos will form the basis for conclusions and findings. Investigators will explore disconfirming evidence and consider possible rival explanations that contrast with study findings and conclusions. Investigators will share preliminary findings with each other on a weekly basis to solicit feedback, including observations and questions.

We will evaluate the intervention components of the system redesign Virtual Collaborative and the data monitoring as well as the implementation strategies at the end of the active implementation stage and again at the end of sustainability. Data obtained during active implementation at earlier sites will be used to modify the ASAP program for subsequent waves, whereas data obtained during the

sustainability period will be used to understand factors associated with sustainable implementation of the ASAP program. Qualitative analyses will involve two qualitative researchers independently reading and re-reading the data, assigning labels and codes to data segments, and developing initial themes from the data. The analysis team will meet to develop consensus on initial themes and related codes from the data, with revision to the themes and codes using an iterative process.

**Categorical data** will be captured by the ASAP research team will include individual-level data (e.g., job position, roles assumed and activities conducted in support of ASAP implementation). We will use NVivo to integrate the tagged qualitative data, the scored construct data, the standardized ORCA data, the categorical data, and the quantitative outcome data in a single, unified project file with multiple codebooks (qualitative, scored constructs, quantitative, categorical). We will use the NVivo “matrix query” feature to explore relationships between the qualitative, construct, quantitative and categorical data, and through this direct cross-referencing of qualitative and quantitative data iteratively analyze how specific combinations of intervention components, implementation strategies and features of local context influence project outcomes. We will also collect data regarding implementation activities proposed and conducted by the sites during the kick-off and throughout active implementation to understand the activities they undertook to conduct quality improvement initiatives related to ASAP. Implementation activities will also be categorized based on their frequency, category (e.g., electronic health record-based), and relative complexity. ASAP analyses will focus both within and across facilities, with special attention to facility- and patient-level factors contributing to increased uptake of the ASAP protocol.

**CFIR and GO Score Ratings** After each 7-month data period, the ASAP research team will meet to conduct CFIR scoring, taking into account memos and information gleaned from data sources outlined in Section 5.6. to score each VAMC with a facility-level valence (i.e., positive, neutral, negative or minimally referenced) and magnitude (i.e., weak or strong) for each CFIR construct. These data sources will also be used to inform GO Score ratings.

As data will be collected longitudinally across, the study team will also identify trends in CFIR and GO Score as they change over time while using memos from such sources as PRIUS calls and External Facilitation calls to understand reasons for change across 7-month data periods. ASAP findings should thus be well-positioned to contribute not only to implementation science but also to the VHA itself as part of a learning healthcare system.

**Case Comparisons** We will use the constant comparison technique to identify emerging themes in the data, including special attention to themes related to context, champions, and external facilitation. Dependent on variability seen between contextual elements, CFIR construct scoring and GO Scores over time, comparisons will be made on higher versus lower performing sites.

Veteran interviews will be conducted at each site to gain the Veteran's perspective on the implementation and their personal experiences as the recipients of local ASAP initiatives.

**Configurational Analysis** draw on concepts from set theory and Boolean algebra to identify conditions that make a difference in reaching an outcome of interest among a defined set of cases.(36, 37) Configurational Comparative Methods (CCMs) offer a set of rigorous, mathematical methods to examine multifactorial causality (i.e., when several variables together have a joint effect on an outcome) as well as equifinality (i.e., several distinct paths leading to the same outcome). CCMs focus on cases, conditions, and combinations rather than variables, and answers research questions like "What combinations of conditions were difference-makers to the outcome of interest?" Configurational approaches have increasingly been used in implementation science and health services research.(21, 38, 39) Within the broader family of CCM approaches, this study applied multi-value Coincidence Analysis (CNA), which offers a systematic approach to build redundancy-free models with small sample sizes and to assess equifinal pathways to implementation success.(21) Factors that will be considered in the configurational analysis will be calibrated after data collection was complete. To develop the analytic dataset for the configurational analysis, we drew on factors collected during the active implementation period of the ASAP trial. The calibration approach is described in Table 1. Whereas some factors are dichotomous (presence/absence, continuous data may be calibrated into quartiles or tertiles.

